#### Acupotomy treatment

Senior traditional Chinese medicine (TCM) doctors with nearly 30 years of clinical experience in acupuncture and 5 years of acupotomology experience will perform all acupotomy procedures. The doctors will not be involved in evaluating the effects of treatment. A flat-head screw-driver-shaped stainless-steel disposable acupotomy needle (0.6 mm in diameter and 50 mm in length, Lejiu Acupotomy Company, China) will be used. Acupotomy will be performed in the lateral position. An iodine antiseptic will be used to sterilize the area for acupotomy. We will not anaesthetize the skin. The needle will be inserted at a position 0.5–1.5 in. away from the spinous process at the T4–T7 level on the painful side of the chest, 50–60 mm under the skin and in a direction parallel to the muscle fibres. The practitioner will stop advancing the acupotomy needle when resistance at the needle point is felt. The practitioner will move the needle point around in different directions to stimulate the soft tissue 3–5 times until the tenderness disappears. Then, the needle will be pulled out, and gauze will be applied to the site to prevent bleeding.

### Outcome measures

When patients are transferred to the PACU, vital signs (heart rate, noninvasive blood pressure, respiratory rate, and SpO_2_) will be monitored and recorded every 5 min for at least 30 min. When the patients’ vital signs are stable and they are able to communicate easily, a series of clinical-scale evaluations and analgesia will be evaluated and recorded. The primary outcome measure of this study is the postoperative pain intensity score. Pain scores (VAS) in the PACU and postoperatively at 1, 2, 4, 8, 12, 24, 48, and 72 h at rest and coughing in each group will be assessed. The VAS ranged from 0 = no pain to 10 = unbearable pain. The mean value and standard deviation will be used for descriptive analysis. The primary outcomes of this study were the resting and dynamic pain scores, which were recorded using a VAS. The secondary outcome measures are postoperative requirements for rescue analgesia, the cumulative amount of self-administered analgesics, the level of sedation (LOS), the Bruggemann comfort scale (BCS), and the functional activity score (FAS) concerning adverse effects and patient satisfaction.

The time to the first rescue analgesic use and the cumulative amount of self-administered analgesics in the first 48 and 72 h will be recorded. The BCS, LOS, and FAS will be recorded at 1, 4, 8, 16, 24, 48, and 72 h after surgery. The LOS is recorded on a 5-point scale, with 0 indicating fully awake, 1 indicating drowsy/closed eyes, 2 indicating asleep/easily aroused with light tactile stimulation or a simple verbal command, 3 indicating asleep/arousable only by strong physical stimulation, and 4 indicating unarousable. The BCS is scored as 0, persistent pain; 1, severe pain while deep breathing or coughing; 2, mild pain while deep breathing or coughing; 3, painless while deep breathing; and 4, painless while coughing. The FAS is scored as A, not restricted; B, mild to moderately restricted; and C, severely restricted. Postoperative adverse effects such as nausea, vomiting, hypotension, hypoxemia, cardiac arrhythmia, and the complications from the drugs and technique will be recorded and treated.

Patient satisfaction will be assessed verbally at 24, 48, and 72 h after surgery using a 5-point Likert scale (5 = completely satisfied, 4 = quite satisfied, 3 = slightly dissatisfied, 2 = dissatisfied, 1 = very dissatisfied). The observer who records the postoperative data will also be blinded to the group assignments.

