### Sample size

Based on the results of our preliminary experiments, the visual analogue scale (VAS) scores (mean difference ± SD) at rest for postoperative day 1 were 3.47 ± 1.39 in the conventional PCA group and 2.34 ± 1.21 in the acupotomy combined with PCA group. We input these data into the G-power 3.1.9.2 software (developed by the University of Düsseldorf, Germany) to calculate the sample size. We obtained a calculated effect size of 0.867 for this outcome after the intervention. A sample size of 70 participants is required to sufficiently detect a target effect size (0.8) with a type 1 error of 5% (*α* = 0.05). Therefore, 70 participants will be recruited, with 35 participants in each group.

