### Statistical analysis

The statistical analysis will be carried out using SAS (SAS 9.2) statistical software. All allocated subjects with available data will be analysed, i.e. on the basis of the intention-to-treat principle. The continuous variables will be presented as the means ± SDs (standard deviations) or the medians (25th to 75th centiles) and compared using the two-tailed Mann-Whitney test or Student’s *t* test, as appropriate. Categorical variables will be presented as numbers and percentages and analysed by Fisher’s exact test or the chi-squared test. Repeated measurements will be analysed using two-way ANOVA, and Tukey’s test will be used for post hoc testing. All statistical tests will be performed with a bilateral test, and *P* ≤ 0.05 will be considered as statistically significant.

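### The primary outcome spans rest and cough pain at nine times with no decisive comparison and no alpha rule between the two conditions, while the sample size covers only resting pain on postoperative day 1

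*Protocol article*

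**What the plan says.** Four places in the protocol article bear on this.

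- **Outcome measures** (and the Methods part of the abstract). The primary outcome is postoperative pain intensity, assessed as "Pain scores (VAS) in the PACU and postoperatively at 1, 2, 4, 8, 12, 24, 48, and 72 h at rest and coughing". The section then adds: "The primary outcomes of this study were the resting and dynamic pain scores, which were recorded using a VAS". Both conditions are therefore primary, at all nine times.
- **Sample size, pilot data.** The basis is VAS "at rest for postoperative day 1". The pilot values "were 3.47 ± 1.39 in the conventional PCA group and 2.34 ± 1.21 in the acupotomy combined with PCA group", and the authors report: "We obtained a calculated effect size of 0.867 for this outcome after the intervention".
- **Sample size, conclusion.** "A sample size of 70 participants is required to sufficiently detect a target effect size (0.8) with a type 1 error of 5" per cent. Power is not stated.
- **Statistical analysis.** Continuous variables are compared by t test or Mann-Whitney test. Repeated measurements go into a two-way ANOVA, with Tukey's test afterwards. All tests are two-sided, and P ≤ 0.05 "will be considered as statistically significant". The section does not say which of these rules, or which ANOVA term, decides the primary outcome. It also does not say whether success is needed at rest, on coughing, on either or on both.

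**The concern.** The error rate and the sample size were set for one comparison: resting pain on one day. The claim the trial may make is wider. As written, a favourable result at rest or on coughing, from whichever term or time shows it, could be reported as a positive primary outcome. The 5% in the Sample size section does not then describe the risk attached to that claim.

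The matter weighs more here than in a blinded trial. The outcome is a subjective score, participants cannot be blinded (Randomization and blinding), and the Discussion concedes that the design does not exclude a placebo effect. An open choice of primary comparison adds a further source of favourable error, one that the plan can remove at no cost in patients.

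**Working it through.** **1. The plan's own figures.** The inputs are from the Sample size section.

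- Difference: 3.47 − 2.34 = 1.13.
- Pooled SD: √[(1.39² + 1.21²)/2] = 1.303.
- Effect size: 1.13/1.303 = 0.867. This agrees with the protocol.
- Sample size at d = 0.8, two-sided 5%, with an assumed power of 90%. The normal approximation gives n per arm = 2(1.960 + 1.282)²/0.8² = 32.8, rounded up to 33, so 66 in total. The noncentral t calculation gives 68. The stated 70 is close to both.
- Because power is not stated, 90% is an inference. By the t calculation, 80% power would need 52 patients and 95% would need 84.
- Power of one two-sided t test with 35 per arm (68 degrees of freedom): at d = 0.8 the noncentrality is 0.8 × √(35/2) = 3.35 and power is 91.0%. At d = 0.867 it is 94.7%.

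So 70 patients suit a single comparison well.

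**2. How many primary values there are.** PACU plus eight postoperative times makes nine; 9 × 2 conditions = 18 scores per patient. The sample size concerns one of them, or a day-1 summary of resting scores.

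**3. False-positive risk if success on either condition counts.** With k independent tests at 5%, the risk is 1 − 0.95^k. Positive correlation lowers it. The documents give no correlations, so the simulations (35 per arm, no true effect) assumed between-time correlations of 0.3 to 0.8 and rest-cough correlations of 0.5 or 0.7. The time-by-time row instead assumes one common correlation of 0.3 to 0.8 among all 18 scores.

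| Reading of the plan | k | Independent | With assumed correlation |
|---|---|---|---|
| One named comparison | 1 | 5% | 5% |
| Group term for rest and for cough | 2 | 9.75% | about 8-9.6% |
| Group and group-by-time terms, both conditions | 4 | 18.5% | about 16-18% |
| t or Mann-Whitney test at each time, both conditions | 18 | 60.3% | about 22-52% |

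The second and third rows follow the planned ANOVA, and the third assumes that the ANOVA is correctly specified for repeated measures. The last row is a reading that the text leaves open. With separate between-time and rest-cough correlations, as in the other rows, it becomes about 25-56%. The closer the rest and cough results are tied, the nearer the second row comes to 5%.

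**4. What the remedies cost in power** (d = 0.8, 35 per arm).

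- One comparison at 0.05: 91.0%.
- Rest and cough at 0.05/2 = 0.025 each: 85.2% for each comparison.

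**The case against.** A reader might infer that the protocol prescribes 18 separate comparisons, each at 5%, with nothing done about multiple times. The text does not support that. VAS at nine times is a repeated measurement, and for such data the Statistical analysis section plans a two-way ANOVA followed by Tukey's test, which is itself a multiplicity adjustment within each ANOVA. The 22-52% range therefore cannot be given as the error rate of this plan. It applies only if the general rule for continuous variables is used at each time.

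A reader might also infer that proper adjustment would destroy the power. Bonferroni over 18 would indeed cut it to 60% at d = 0.8, but nothing in the plan calls for that correction, and it ignores the correlation between scores. Splitting alpha between rest and cough keeps 85%.

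Two further objections are fair. Resting day-1 pain is part of the declared primary outcome, so the sample size is incompletely aligned with it rather than aimed at something else. And the decisive ANOVA term and Tukey's comparison family may be left to an analysis plan that is not shown, so their absence is not the finding.

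What stands is in the article's own text. Two conditions are declared primary at nine times, the trial is sized on one condition at one time, and nothing links rest and cough. Tukey's test works inside one ANOVA and does not cover that last gap. A rule that both conditions must succeed would avoid the inflation, but none is stated.

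**Conclusion.** The point holds in this form: the primary outcome has no single decisive comparison and no alpha rule across its two conditions, while the sample size and its 5% error relate only to resting VAS on postoperative day 1.

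Under the planned ANOVA, with success on either condition, the risk is about 8-10% for two group tests and about 16-18% if group-by-time terms also count. The figure of roughly 22-52% is a conditional upper scenario for time-by-time testing. The exact values depend on assumed correlations; for independent tests the limits of 9.75%, 18.5% and 60.3% follow from the number of tests alone. The 91% power is calculated here, since the protocol states none.

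The sample size arithmetic is not in question.

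**What to change.** Name one primary comparison: resting VAS on postoperative day 1, between groups, two-sided at 5%. The sponsor must confirm that the pilot's day-1 value is the 24 h score. That is the natural reading of the assessment schedule, but the article does not say so, and a day-1 average is also possible.

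Make the other resting times and all coughing scores secondary. Keep them in the planned repeated-measures analysis and report them with 95% confidence intervals. Cough VAS at the same time may be tested next in a fixed order, only if the primary comparison succeeds.

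Alternatively, keep rest and cough as co-primary outcomes at 0.025 each on the same named comparison. Power is then 85% at d = 0.8 for each. The article gives no pilot figure for coughing, so for that condition the 0.8 would be an assumption.

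Either way, amend the abstract, Outcome measures and Statistical analysis text before any unblinded look at the data.

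The cost is wording only, and N stays at 70. The downside is that an isolated difference at another time or condition can no longer be claimed as a primary result.

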**Methods:**

The study will be a single-centre, parallel group, randomized controlled trial.

Seventy patients with significant pain after thoracoscopic surgery with a visual analogue scale (VAS) score ≥ 7 will be included and randomly distributed into two groups: G1, the acupotomy combined with PCA group; and G2, the conventional PCA group. The primary outcome measure is pain scores at rest and coughing evaluated with the VAS by a blinded observer in the postanaesthesia care unit (PACU) and postoperatively at 1, 2, 4, 8, 12, 24, 48, and 72 h. The secondary outcome measures are postoperative requirements for rescue analgesia, the cumulative amount of self-administered analgesics, the level of sedation (LOS), the Bruggemann comfort scale (BCS), and the functional activity score (FAS) concerning adverse effects and patient satisfaction.

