## Methods

### Study design and setting

This study will use a single-centre, parallel group, randomized controlled trial to explore the efficacy and safety of acupotomy combined with PCA for the treatment of pain after VATS. The study will be carried out at Fujian Provincial Hospital and has been registered with the Chinese Clinical Trial Registry (ChiCTR1900027191).

After eligibility screening and written informed consent provision, eligible participants after thoracoscopic surgery will be randomly distributed into two postoperative analgesia groups: G1, the acupotomy combined with PCA group; and G2, the conventional PCA group. In addition to the abovementioned analgesic regimen, all subjects will receive conventional postoperative treatment, including health education and conventional medical therapy. This protocol design adheres to the Standard Protocol Items: Recommendations for Interventional Trials (SPIRIT) Checklist (Additional file 1). The flow diagram for this trial is presented in Fig. 1.

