### Participants and eligibility criteria

Competent doctors will strictly screen qualified subjects according to inclusion and exclusion criteria.

Seventy patients with lung cancer, an American Society of Anesthesiologists physical status I–II, an age of 30–70 years, and a VAS score ≥ 7 who are selected for VATS lobectomy will be recruited for this clinical study. They will also be required to be able to communicate well and understand how to score their pain level. All eligible participants who meet the study inclusion criteria will be identified through the Division of Thoracic Surgery. The study exclusion criteria are coagulation disorders; neuropathy; infections at the site of acupotomy; obesity (body mass index, BMI > 30 kg/m^2^); clinically significant neurological, cardiovascular, renal, and hepatic diseases; an inability to remove the tracheal catheter or to correctly use the PCA pump after surgery; psychiatric illnesses that would interfere with the perception and assessment of pain; and pain-killer use within a week before surgery.

We will have dedicated researchers to screen existing institutional registry records and databases and to work closely with the thoracic surgeons to identify qualified participants. Once eligibility is established, the research staff will contact eligible participants or their families and explain the purpose and significance of this study, provide full explanations to eliminate participants’ doubts, and ascertain interest in enrolment. If a participant agrees to enrol, informed consent will be obtained. Participants will undergo baseline assessments following informed consent provision. A CONSORT diagram of participant recruitment is shown in Table 1.

**Table 1 Tab1:** Trial process chart

Items	Before enrollment -2-1 (weeks)	PACU	Postoperative 1 h	Postoperative 2 h	Postoperative 4 h	Postoperative 8 h	Postoperative 12 h	Postoperative 24 h	Postoperative 48 h	Postoperative 72 h
Inclusion criteria	×									
Exclusion criteria	×									
Informed consent	×									
Randomization and allocation	×									
**Pain scores** (VAS)		×	×	×	×	×	×	×	×	×
Postoperative requirements for rescue analgesia		×	×	×	×	×	×	×	×	×
LOS		×	×	×	×	×	×	×	×	×
BCS		×	×	×	×	×	×	×	×	×
FAS		×	×	×	×	×	×	×	×	×
Cumulative amount of self-administered analgesics								×	×	×
Adverse events		×	×	×	×	×	×	×	×	×
Patients’ satisfaction								×	×	×

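### The protocol does not fix when the qualifying VAS of at least 7 is taken, counts the PACU score as a primary outcome whichever it is, and states no baseline term

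*Protocol article*

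**What the plan says.** **Entry criterion.** The Abstract (Methods) states "Seventy patients with significant pain after thoracoscopic surgery with a visual analogue scale (VAS) score ≥ 7 will be included" and then randomized, so the threshold refers to pain after surgery. Participants and eligibility criteria repeats the threshold without a time: "a VAS score ≥ 7 who are selected for VATS lobectomy will be recruited for this clinical study". Neither place says whether the score is at rest or on coughing.

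**Randomization.** Study design and setting places it after the operation: "eligible participants after thoracoscopic surgery will be randomly distributed into two postoperative analgesia groups". Table 1 ticks inclusion, exclusion, consent and randomization only in the column for the weeks before enrolment, and first ticks the VAS in the PACU column.

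**Baseline.** Participants and eligibility criteria says "Participants will undergo baseline assessments following informed consent provision". It does not list what these are, and no baseline VAS is named.

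**Outcome.** Outcome measures lists "Pain scores (VAS) in the PACU and postoperatively at 1, 2, 4, 8, 12, 24, 48, and 72 h", at rest and on coughing, as the primary pain scores. The PACU scales are taken once vital signs are stable and the patient can communicate easily.

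**Treatment.** The anaesthesia and PCA section connects controls to the pump immediately after surgery. In the other arm acupotomy comes before PCA. Neither step is ordered against the PACU score.

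**Analysis.** Statistical analysis says continuous variables will be "compared using the two-tailed Mann-Whitney test or" Student's t test, with two-way ANOVA and Tukey's test for repeated measurements. No baseline term appears.

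**The concern.** A score used to admit patients is a baseline. If both arms must reach 7 before treatment, any difference between them at that time is chance, and the score says nothing about acupotomy. Counted as an outcome time, it pulls an average over time towards zero. Left out of the model, it is not used to correct chance imbalance in starting pain or to reduce residual variance in a trial of 70.

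The schedule invites this confusion because the PACU score is the first VAS it contains. The pre-enrolment column cannot hold a postoperative score, so the PACU is the only scheduled time early enough to be a candidate for the qualifying score. The same score is listed as an outcome. The protocol has to say which role it plays, because the correct analysis differs between the two.

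**Working it through.** **1. The plan's own figure.** The sample size section gives day-1 rest VAS of 3.47 (SD 1.39) and 2.34 (SD 1.21).

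- Pooled SD = √((1.39² + 1.21²)/2) = 1.303.
- d = (3.47 − 2.34)/1.303 = 1.13/1.303 = 0.867, as stated.
- At the target d = 0.8, 35 per arm and two-sided 5%, t-test power is 0.910. The protocol states no power. For two-sided 90% the t test needs 68 in total, close to the planned 70.

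This calculation uses one time point, so the role of the PACU score does not touch it.

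**2. Order of events.** The Abstract and Study design give: surgery, VAS of at least 7, randomization, acupotomy in one arm. On that order the qualifying score precedes acupotomy. Table 1 gives: eligibility and randomization, surgery, first VAS in the PACU. On that order a postoperative threshold cannot be applied before allocation. The two cannot both hold.

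**3. If the PACU score is the qualifying score.** Assume the same difference δ at the eight later times and zero at the PACU.

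- Nine-time average = (8δ + 0)/9 = 0.889δ, a loss of 1/9 = 11.1%.
- For power, assume equal variances and a common within-patient correlation ρ. The variance of a mean of k times, relative to one time, is (1 + (k − 1)ρ)/k.

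| Assumed d per time | Assumed ρ | Power, eight times | Power, nine times |
|---|---|---|---|
| 0.8 | 0.5 | 0.993 | 0.976 |
| 0.8 | 0.7 | 0.970 | 0.928 |
| 0.5 | 0.5 | 0.785 | 0.691 |
| 0.5 | 0.7 | 0.670 | 0.572 |

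For example, with d = 0.5 and ρ = 0.5 the eight-time effect is 0.5/√0.5625 = 0.667, and the nine-time effect is 0.444/√0.5556 = 0.596. A score confined to 7–10 would probably vary less than the others, so the powers are illustrative. The 8/9 factor does not depend on that.

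**4. If the PACU score follows treatment.** It is not confined to 7–10 and can carry an effect, so there is no built-in dilution. Adjusting for it could remove part of the treatment effect.

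**5. What a true baseline would add.** Adjustment multiplies residual variance by 1 − r², so the effective d is 0.8/√(1 − r²). The documents give no r. Restriction to 7–10 lowers it: r_restricted = r·u/√(r²u² + 1 − r²), where u is the ratio of restricted to unrestricted SD. Unrestricted scores are assumed normal with mean and SD of 5 and 2, 6 and 2, or 7 and 1.5, giving u = 0.36, 0.39 and 0.50. An unrestricted r of 0.3 to 0.7 then becomes about 0.11 to 0.44.

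| r after restriction | 1 − r² | Effective d | Power, 35 per arm |
|---|---|---|---|
| 0 | 1.000 | 0.800 | 0.910 |
| 0.11 | 0.988 | 0.805 | 0.913 |
| 0.20 | 0.960 | 0.816 | 0.920 |
| 0.44 | 0.806 | 0.891 | 0.957 |

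The gain runs from 0.913 − 0.910 = 0.003 to 0.957 − 0.910 = 0.047, that is, about 0 to 5 points.

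**The case against.** The strongest reply is that nothing in the protocol places the PACU score before treatment. Controls are connected to PCA straight after surgery, and the PACU scales wait until the patient is stable and can communicate. The score may well come after PCA has started and, in the other arm, after acupotomy. The unspecified baseline assessments leave room for a separate qualifying score. All of this stands.

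A reader might therefore infer too much in three ways:

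- *That the plan dilutes the treatment effect.* It does so only if the PACU score is the qualifying one, and only for an effect averaged over time. The per-time tests and the day-1 contrast are untouched.
- *That an equal first level creates a spurious group-by-time interaction.* It does not. If the arms are equal at a true baseline and differ later, the interaction reflects the treatment effect.
- *That a valuable covariate is being thrown away.* Range restriction keeps the gain small, and the PACU score may be used this way only if it precedes treatment.

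It can also be said that an unadjusted comparison in a randomized trial is valid and that covariates are often left to the analysis plan. That is fair, and it limits the adjustment to an improvement in efficiency. It does not answer the contradiction over timing or the double role of the PACU score, both of which are in the protocol's own text.

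**Conclusion.** The point holds as a timing defect with a conditional analytic consequence. It is firm that the text and Table 1 disagree on when eligibility and randomization occur, that no VAS is scheduled before the PACU, that the PACU score is a primary outcome time, and that the stated analysis has no baseline term.

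It is not established that the PACU score is the qualifying score. If it is, a group effect averaged equally over nine times shrinks by about 11%, assuming a constant effect at the eight later times. If it is not, the score that defines the population is missing from the schedule. Either way the protocol should be corrected.

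The gain from baseline adjustment is about 0 to 5 points of power on 0.910 at d = 0.8, resting on assumed correlations and an assumed unrestricted pain distribution, plus correction of chance imbalance. This is worth doing because it costs little. It does not undermine the trial.

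**What to change.** 1. Reconcile the Abstract, Study design and setting, Participants and eligibility criteria (with Table 1), the anaesthesia and PCA section, and Outcome measures on when the qualifying VAS is taken relative to randomization, acupotomy, PCA and the PACU outcome score.
2. State whether the threshold of 7 refers to rest or coughing.
3. Show the pre-randomization qualifying VAS in Table 1 as baseline and exclude that score from the primary outcome times. If the PACU score is a separate, post-treatment score, keep it as an outcome and do not adjust for it.
4. Include the baseline VAS as a covariate in the primary comparison and in the repeated-measures model.

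**Cost.** If the PACU score is the qualifying score, this is wording and one model term. If it is not, it also needs one more field in the case report form. No change to analgesic management is proposed.
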